### Outcome measures

The primary outcome of the study is to develop and validate the Brillouin and SERS/Raman spectroscopy for non-contact urinary protein detection and protein profiling in patients with nephrotic syndrome. The secondary outcome of the study is identifying the most hazarded protein profiles associated with adverse outcomes.

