## Abstract

**Background:**

Proteinuria is a major marker of chronic kidney disease (CKD) progression and the predictor of cardiovascular mortality. The rapid development of renal failure is expected in those patients who have higher level of proteinuria however, some patients may have slow decline of renal function despite lower level of urinary protein excretion. The different mechanical (visco-elastic) and chemical properties, as well as the proteome profiles of urinary proteins might explain their tubular toxicity mechanism. Brillouin light scattering (BLS) and surface enhanced Raman scattering (SERS) spectroscopies are non-contact, laser optical-based techniques providing visco-elastic and chemical property information of probed human biofluids. We proposed to study and compare these properties of urinary proteins using BLS and SERS spectroscopies in nephrotic patient and validate hybrid BLS-SERS spectroscopy in diagnostic of urinary proteins as well as their profiling. The project ultimately aims for the development of an optical spectroscopic sensor for rapid, non-contact monitoring of urine samples from patients in clinical settings.

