**Methods:**

BLS and SERS spectroscopies will be used for non-contact assessment of urinary proteins in proteinuric patients and healthy subjects and will be cross-validated by Liquid Chromatography-Mass Spectrometry (LC-MS). Participants will be followed-up during the 1 year and all adverse events such as exacerbation of proteinuria, progression of CKD, complications of nephrotic syndrome, disease relapse rate and inefficacy of treatment regimen will be registered referencing incident dates. Associations between urinary protein profiles (obtained from BLS and SERS as well as LC-MS) and adverse outcomes will be evaluated to identify most unfavored protein profiles.

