### Participants

The 80 patients with proteinuria will be recruited form National Scientific Medical Center, admitted to the internal medicine department. Age and gender matched 20 healthy volunteers will be enrolled from the outpatient clinics. The inclusion criteria are both male and female patients with any ethnic group, aged between 18 and 65 years old and newly diagnosed patients with glomerulonephritis and different range of proteinuria. The following exclusion criteria will be used: patients aged < 18 and > 65 years, glomerular filtration rate (GFR) < 60 ml/min, pregnant females, patients with diabetes mellitus, cancer, infectious diseases, and other life-treating comorbidities/conditions. Clinical and demographics data of the participants, medical history, comorbidities and data related to the disease will be recorded in case report forms.

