Summarizing the available relevant literature and emphasizing the scientific novelty and significance of dual Brillouin-SERS spectroscopy, we will try to study and cover following question in this proposed project: Do non-contact dual Brillouin-SERS spectroscopy provide differential and diagnostic information on mechano-chemical profile of urine and urinary protein in healthy subjects and patients with different range of proteinuria?

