### Expected science & technology, social & economic impacts

In case of successful development of non-contact hybrid Brillouin-SERS sensing tool and its clinical deployment for diagnosis and prognosis of proteinuria, we expect its application for diagnosis and prognosis of other renal diseases of patients with abnormalities related not just to high protein loss, but also to elevated concentration of urea, creatinine, uric acid and other components. The impact of to-be-developed optical instrumentation and knowledge base is also envisioned in other areas of biomedical sciences and medicine, including biophotonic sensing of viruses, where non-invasive optical diagnostics and imaging is currently in high demand.

Young scientists in Kazakhstan will be trained in important multidisciplinary areas spanning from nephrology to biomedical photonics & engineering, laser-optical instrumentation design and construction, spectroscopy, biomechanics, biorheology and biochemistry of human fluids. By the end of 3-year project we expect:
to develop basic science foundation for measurement and analysis of visco-elastic and chemical properties of human urine and urine proteins of patients having various degree of proteinuria.to construct, optimize and test the hybrid Raman-Brillouin spectroscopy sensing system for non-contact simultaneous monitoring of visco-elastic and chemical properties of urine samples taken from healthy subjects and patients with different range of proteinuria and other kidney diseases related to elevated concentration of urea, creatinine and uric acid and cross-validate them with LC-MS.to identify the most important types of urine proteins based on their visco-elasticity, amino-acid profile and molecular weight responsible for the most severe cases of proteinuria and progressive renal function decline.to reach a roadmap for translating hybrid Brillouin-Raman sensor as a new diagnostic & prognostic tool in patients with proteinuria to a clinical setting and its potential deployment to other biomedical applications.to report research results in at least 3 international conferences and publish at least 5 papers in peer-reviewed international journals with high impact factors.to train young Kazakh medical and physical scientist in advanced inter-disciplinary areas of nephrology & biophotonics.

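### The primary outcome names nephrotic syndrome, but eligibility, the research question and the ROC analysis use a broader group with varying proteinuria

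*Protocol article*

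**What the plan says.** The Outcome measures section sets the primary outcome as development and validation of Brillouin and SERS/Raman spectroscopy for "non-contact urinary protein detection and protein profiling in patients with nephrotic syndrome". The Background paragraph of the Abstract has the same narrow target: the urinary proteins are to be studied "using BLS and SERS spectroscopies in nephrotic patient".

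The Participants section describes a different group. "The 80 patients with proteinuria will be recruited", and the inclusion criterion is "newly diagnosed patients with glomerulonephritis and different range of proteinuria". Patients with GFR below 60 ml/min are excluded. No inclusion or exclusion criterion mentions nephrotic syndrome or sets a minimum level of proteinuria. In addition, "Age and gender matched 20 healthy volunteers will be enrolled from the outpatient clinics".

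The Methods paragraph of the Abstract follows the wider description: "non-contact assessment of urinary proteins in proteinuric patients and healthy subjects". So does the research question in the Discussion, which asks whether the technique is informative "in healthy subjects and patients with different range of proteinuria". The Statistical analysis section correlates the spectroscopy with LC-MS and clinical data in patients and healthy participants, and uses ROC curves to find cut-offs that predict high proteinuria.

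**The concern.** The population named in the primary outcome is not the population that the criteria select or the analysis uses. For a validation study this matters, because accuracy and correlation depend on the mix of people in whom they are measured. A sensor that separates healthy urine from heavily proteinuric urine can look good across the whole sample and still discriminate poorly among nephrotic patients.

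If the plan is followed literally, the main result will come from mixed proteinuria plus healthy volunteers and be presented as validation in nephrotic syndrome. The reader of the final report could not tell from the stated outcome to whom the result applies.

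**Working it through.** The plan states no power, effect size or precision for the primary outcome, so there is no figure to reproduce. The check is a comparison of the text.

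**1. Population by section**

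| Section | Population |
|---|---|
| Outcome measures (primary) | nephrotic syndrome |
| Abstract, Background | nephrotic patients |
| Participants | newly diagnosed glomerulonephritis, varying proteinuria, no nephrotic criterion; 20 healthy volunteers |
| Abstract, Methods | proteinuric patients and healthy subjects |
| Statistical analysis | patients and healthy participants; ROC target is high proteinuria |
| Discussion, research question | healthy subjects and patients with varying proteinuria |

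Two places use the narrow population. The sections that select participants, pose the question and specify the analysis use the wide one.

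**2. Can the planned ROC analysis serve the narrow population?** Sensitivity needs participants with high proteinuria, and specificity needs participants without it. The article does not give the cut-off for high proteinuria. If nephrotic-range proteinuria counts as high, a nephrotic-only set contains no non-cases, so specificity and AUC cannot be estimated. The analysis as stated therefore relies on the wider population.

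**3. Does performance carry over from wide to narrow?** Limiting the sample to nephrotic patients removes the healthy volunteers and the patients with little proteinuria, so the spread of protein values shrinks. If the spectroscopic reading is linear in protein with constant error variance, the correlation is lower in the sample with the smaller spread. The direction is clear. The amount cannot be stated, since the documents give no standard deviations.

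**4. How many patients match the stated outcome?** The nephrotic share of the 80 is not given. Over an assumed range of 25%, 50% and 75%:

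- 0.25 × 80 = 20, 0.50 × 80 = 40, 0.75 × 80 = 60 patients.

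For the planned correlations, the 95% half-width on the Fisher z scale is 1.96/√(n − 3):

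- n = 80: 1.96/√77 = 0.22
- n = 60: 1.96/√57 = 0.26
- n = 40: 1.96/√37 = 0.32
- n = 20: 1.96/√17 = 0.48

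These values only illustrate how precise a nephrotic subgroup might be. They apply to Pearson correlations; the plan also allows Spearman's.

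**The case against.** The strongest reply is that the working plan is coherent. Selection, the LC-MS comparison, the correlations, the ROC analysis and the research question all use everyone enrolled, and no section directs a nephrotic-only analysis. On this view the narrow wording is a loose label in one outcome statement and one abstract sentence. If a nephrotic analysis is intended, its definition may sit in a fuller protocol or SAP that is not shown.

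Much of this stands. The lack of a subgroup definition in the article is not held against it. What remains is that the article states both the target population and the entry criteria, and they disagree. The label is on the primary outcome, which determines what the study may claim.

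Some stronger readings are tempting but not supported:

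- **That nephrotic patients are not enrolled.** They are not excluded. Those with newly diagnosed glomerulonephritis who meet the other criteria can enter, so the named population may be a subset of the enrolled one.
- **That the loss can be expressed as wider confidence intervals for sensitivity, starting from all 80 patients.** The planned sensitivity is for predicting high proteinuria. Its denominator is participants with high proteinuria, not all 80, and the plan assumes no sensitivity value.
- **That relapse, as an outcome, concerns nephrotic patients only.** The Statistical analysis section lists the disease relapse rate separately from complications of nephrotic syndrome, and the enrolled disease is glomerulonephritis. Nothing there limits relapse to a nephrotic subset.
- **That the project deliverable is a further primary target.** The text on patients with "proteinuria and other kidney diseases related to elevated concentration of urea, creatinine and uric acid" stands in the Discussion among expected results. It is not an outcome or an eligibility criterion, and it does not affect the primary analysis.

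**Conclusion.** The point holds as a contradiction in stated text. The primary outcome claims validation in nephrotic syndrome, while the entry criteria, the research question and the ROC analysis concern newly diagnosed glomerulonephritis with varying proteinuria, compared with healthy volunteers. Results in the enrolled sample would not by themselves support the claim for nephrotic patients.

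No stated number is wrong, and the study can run as designed. What changes is the population to which its main conclusion may be applied. The 20 to 60 matching patients rest wholly on the assumed share. The conclusion does not depend on that share unless nearly every recruited patient turns out to be nephrotic, which would sit badly with the stated intention to enrol differing levels of proteinuria. It should be corrected before results are reported.

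**What to change.** - **Reword the primary outcome**, and the matching sentence in the Abstract, to the enrolled population: patients with newly diagnosed glomerulonephritis and varying proteinuria, GFR 60 ml/min or above, with healthy comparators. Analyse all enrolled participants for it.
- **Name nephrotic-range patients as a pre-specified subgroup.** Define it from the proteinuria, ACR and PCR already measured at enrolment, fix the definition before the spectroscopy data are examined, and report performance within it separately. Keep relapse and the other adverse outcomes open to all patients.
- **Minor:** align the deliverable on other kidney diseases with who is enrolled, or mark it as future work.

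The cost is a wording amendment, with no added patients, samples or tests. The headline claim no longer names nephrotic syndrome, and whatever is said about nephrotic patients rests on a smaller and less precise subgroup.

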### Statistical analysis

All statistical analyses will be performed using STATA MP Version 15 (STATA Corporation, College Station, TX) statistical package. Two-sided *P-*values less than 0.05 will be reported as a significant for all analyses. Mean ± standard deviation (SD) for normal and median - interquartile range (IQR) for abnormal distribution of numerical variables will be shown in all data. Categorical variables will be presented as numbers (percentage). Categorical variables will be compared using Chi-square test or Fisher’s exact test and continuous variables will be compared using Kruskal–Wallis and/or Mann–Whitney U-test, as appropriate. Comparison of repeated two or more variables will be assessed with Wilcoxon and/or Friedman test as appropriate.

Obtained measurements of urinary protein by Brillouin and SERS/Raman spectroscopy will be compared with LC-MS data from same participant urine samples. Correlation between Brillouin and SERS/Raman spectroscopy parameters, LC-MS data and clinical-laboratory data of patients as well as healthy participants will be provided using Pearson’s or Spearman’s correlation as appropriate.

Univariate logistic regression will be used to test the association of several risk factors with high level of proteinuria. Multivariate logistic regression analysis will be used to assess the predictors for adverse outcomes. A receiver operator characteristics curve (ROC curve) analysis will be performed to identify the sensitivity, specificity, negative and positive predictive values of cut-off levels of Brillouin and SERS/Raman spectroscopy parameters in prediction of high proteinuria. Between measurement comparison of AUC will be provided with method developed by DeLong et al. [25].

During 1 year of follow-up, all adverse events such as exacerbation of proteinuria, progression of CKD, complications of nephrotic syndrome (thrombosis, nephrotic crisis, infection, including death), disease relapse rate and inefficacy of treatment regimen will be registered with referencing incident dates. Unadjusted and adjusted regression models will be evaluated to identify the association between urinary protein profiles defined by Brillouin and SERS/Raman spectroscopy and abovementioned adverse outcomes.

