### Liquid chromatography-mass spectrometry

A reversed-phase LC-MS will perform for profiling of urine protein. LC-MS system consists of a Dionex HPLC pump (Ultimate 3000 RSLCnano System, Thermo Scientific) and UHR-QqTOF mass spectrometer Impact II (Bruker). Protein sample will be injected through trapping column setup Acclaim PepMap100 C18 5 mm × 300 um pre-column (Thermo Scientific) and peptides separated on an analytical Acclaim Pep-Map 15 cm x 75um RSLC column (Thermo Scientific) using 75 min multistep acetonitrile gradient (buffer A: 0.1% FA; buffer B 90%ACN/ 10% H2Oin 0.1% FA) at a flow rate of 0.3 ul/min. Data analysis will be performed through Mascot software using the SwissProt protein database. Furthermore, protein samples differentiated according to their molecular weights will be separately assessed by dual Raman-Brillouin hybrid system for comparative mechano-chemical characteristics and correlations.

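### A single 0.05 threshold is applied to every analysis, with no multiplicity control, and its results are used to select the most harmful urinary protein profiles

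*Protocol article*

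**What the plan says.** The Statistical analysis section of the protocol article sets one rule for the whole study: two-sided P-values "less than 0.05 will be reported as a significant for all analyses". The same section then lists what the rule applies to:

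- group comparisons and repeated-measure comparisons;
- the "Correlation between Brillouin and SERS/Raman spectroscopy parameters, LC-MS data and clinical-laboratory data of patients as well as healthy participants";
- univariate logistic regression for high proteinuria and multivariate logistic regression for adverse outcomes;
- ROC cut-offs for the optical parameters, with DeLong comparisons of AUC;
- unadjusted and adjusted regression of protein profiles on the adverse outcomes.

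The outcomes registered over one year are "all adverse events such as exacerbation of proteinuria, progression of CKD, complications of nephrotic syndrome (thrombosis, nephrotic crisis, infection, including death), disease relapse rate" and, as a fifth kind, failure of the treatment regimen. Under Outcome measures, "The secondary outcome of the study is identifying the most hazarded protein profiles associated with adverse outcomes". The section on expected impacts in the Discussion adds the aim of identifying the protein types behind severe proteinuria and declining renal function.

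The Participants section describes one cohort: "The 80 patients with proteinuria will be recruited", and "Age and gender matched 20 healthy volunteers will be enrolled from the outpatient clinics". The article names no primary optical parameter, protein feature or adverse outcome. It does not give the number of parameters, proteins or tests, and it does not label any of these analyses exploratory.

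**The concern.** The secondary outcome is a search: many candidate features are related to several outcomes, and those that pass are named as harmful. A threshold that limits the error of one test does not limit the error of such a search. Each further parameter, outcome or model adds another 5% chance of a false flag where no association exists, and the search reports exactly the results that cross the line.

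The article describes no second cohort in which flagged profiles would be checked. A reader of the results would therefore see a list of significant profiles from 80 patients and could not tell how many are chance. What is at stake is the credibility of the secondary outcome. The primary aim, validating the spectroscopy against LC-MS, depends mainly on the size of correlations and accuracy measures and is less affected.

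**Working it through.** The article gives no power, family-wise error or sample-size calculation, so there is no figure of its own to reproduce. The level of 0.05 is read directly from the text.

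**Inputs from the article:** two-sided level 0.05; 80 patients; at least five kinds of adverse outcome.

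**Assumed, because the article does not state them:** number of tests *m*; share *π* of tested associations that are real; event rate 20–40%; standardised difference *d* of 0.5–0.8; independent tests.

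**Step 1. Chance of at least one false positive, all nulls true.** Formula: 1 − 0.95^m. Expected number of false positives: 0.05 × m.

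| m | At least one false positive | Expected number |
|---|---|---|
| 5 (one feature, five outcomes) | 1 − 0.95^5 = 22.6% | 0.25 |
| 20 | 1 − 0.95^20 = 64.2% | 1.0 |
| 50 | 1 − 0.95^50 = 92.3% | 2.5 |

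The first row needs no assumption about how many parameters or proteins are measured. Positive correlation between features or outcomes would lower the middle column but not the last.

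**Step 2. Share of significant results that are false.** Formula: 0.05(1 − π) / [0.05(1 − π) + power × π].

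Power for one feature against a binary outcome is approximately Φ(d√(n₁n₂/80) − 1.96), where n₁ and n₂ are patients with and without the event. With a 20% event rate and d = 0.5, this is Φ(0.5 × √(16 × 64/80) − 1.96) = 43%. With 40% and d = 0.8, it is Φ(0.8 × √(32 × 48/80) − 1.96) = 94%. Across that range:

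| Share of associations that are real | False share of significant results |
|---|---|
| 1% | 84–92% |
| 5% | 50–69% |
| 10% | 32–51% |
| 20% | 18–32% |

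**Step 3. Where chance findings become a majority.** Setting the share to one half gives π = 0.05 / (0.05 + power). At 50% power, π = 0.05/0.55 = 9.1%. At 90% power, π = 0.05/0.95 = 5.3%. Chance findings outnumber real ones only if the real share is below that value.

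**Step 4. Cost of the strictest correction.** With a 30% event rate and d = 0.8, power at 0.05 is about 91%. A Bonferroni threshold for 100 tests (0.05/100 = 0.0005) lowers it to about 42%. This is why false-discovery-rate control, which is less severe, suits a screen of this kind better.

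**The case against.** The strongest reply is that the sentence only fixes a level and sidedness. It does not say that the P-values are unadjusted, and a 0.05 level is compatible with adjusted P-values. How families are defined and corrected is often left to an analysis plan, which is not shown here. Part of this stands: such a plan may exist. But the sentence covers all analyses without exception and mentions no adjustment, so a reader who follows it will apply 0.05 test by test. That is a stated rule that can be corrected, and more than a missing detail.

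The number of tests may also be small. The article speaks of parameters and profiles, not of individual spectral peaks. The Brillouin measurement in the Discussion rests on two quantities, peak position and width. The LC-MS text says "Data analysis will be performed through Mascot software using the SwissProt protein database", which concerns identification and not hypothesis testing, and proteins may be grouped by molecular weight. The Abstract includes LC-MS profiles in the outcome associations, whereas the closing sentence of the Statistical analysis section names only the optical methods. A reader might infer a screen of hundreds of single proteins with dozens of false hits, but the article does not plan one. This objection stands against any large count. It does not remove the problem, since five tests already give 22.6%.

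Finally, this is the secondary aim of an observational study, and the article ties no treatment decision to it. That lowers the severity.

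**Conclusion.** The concern holds in a limited form. The article applies an uncorrected 0.05 rule to several families of measurement and at least five kinds of outcome, and uses the associations to select harmful profiles. With independent true nulls, the chance of a false positive is 22.6% for one feature against five outcomes and 64% for 20 tests. An unknown and possibly majority share of the flagged profiles may be chance findings. A majority requires that fewer than roughly 5–9% of tested associations are real, on assumed power of 50–90%.

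A reader might go further and conclude that the selected proteins will mostly be chance findings and will mostly fail to replicate. The article does not support this: it gives neither the number of tests, nor the share of real associations, nor the power, and at a 20% real share the false share is 18–32%. Nor does it say that outcome P-values decide what is built into the sensor, which is described as optical hardware. The point should be fixed and is a cheap improvement; it does not undermine the study.

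**What to change.** Replace the sentence on significance with a rule along these lines. Each test is assigned in advance to one family: optical parameters, LC-MS protein features, or adverse-outcome associations. Within a family, a result is called significant only if it passes the Benjamini–Hochberg procedure at a false discovery rate of 5%. All other results are reported as estimates with 95% confidence intervals and labelled exploratory. The families and their members should be listed before outcome data are examined. If an analysis plan already contains such a rule, the article's sentence should be brought into line with it.

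The cost is one paragraph of wording, with no extra patients or assays. Fewer associations will be labelled significant, and power for any single association will be somewhat lower, though less so than under the Bonferroni correction shown above.

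### Healthy volunteers are matched on age and gender, but the group tests named in the plan ignore both; where age or sex affects a reading, the patient-versus-healthy comparison is conservative and loses some power

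*Protocol article*

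**What the plan says.** The Participants section sets the two groups: "The 80 patients with proteinuria will be recruited form National Scientific Medical Center", and "Age and gender matched 20 healthy volunteers will be enrolled from the outpatient clinics". It does not say whether each volunteer is tied to particular patients or whether the volunteers as a group follow the patients' age and gender distribution.

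The Statistical analysis section names the group tests: "Categorical variables will be compared using Chi-square test or Fisher’s exact test", and "continuous variables will be compared using Kruskal–Wallis and/or Mann–Whitney U-test, as appropriate". Tests for dependent data appear once, for a different purpose: "Comparison of repeated two or more variables will be assessed with Wilcoxon and/or Friedman test as appropriate". The regression models in that section address high proteinuria and adverse outcomes during follow-up, not the difference between patients and volunteers. The significance rule is "Two-sided *P-*values less than 0.05 will be reported as a significant for all analyses".

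The Discussion states the study question as whether the optical method gives differential and diagnostic information on the "mechano-chemical profile of urine and urinary protein in healthy subjects and patients with different range of proteinuria".

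**The concern.** The design uses age and gender to choose the volunteers, and no analysis named for the patient-versus-healthy comparison then uses them. If age or sex drives part of a reading, matching removes that part from the difference between the groups. An independent-groups test still counts it as random noise, so the standard error implied by the test exceeds the true one.

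What is at stake is sensitivity. With 20 volunteers, the healthy group limits the precision of this comparison. A modest real difference in a Brillouin, SERS/Raman or LC-MS reading could be missed although the same samples could show it.

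**Working it through.** **Inputs from the protocol article.** 80 patients and 20 volunteers (Participants); two-sided 0.05 (Statistical analysis). No effect size, SD, power or correlation is stated, so there is no planned figure to reproduce.

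**Assumptions.** Normal readings with SD 1 within each group; true difference d = 0.7 SD (1.5 SD as the large case); frequency matching, with volunteers following the patients' age and sex distribution; age and sex together explain a share R² of the within-group variance.

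**Step 1: baseline.** Independent-groups SE = √(1/20 + 1/80) = 0.25. At d = 0.7, 0.7/0.25 = 2.80 and 2.80 − 1.96 = 0.84, so power is about 80% by the normal approximation.

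**Step 2: effect of matching.** With age and sex balanced by design, the true SE of the difference is about 0.25 × √(1 − R²), while an unadjusted test goes on using about 0.25. Hence:
- false-positive rate of the unadjusted test ≈ 2 × [1 − Φ(1.96/√(1 − R²))]
- power of the unadjusted test ≈ Φ((d − 0.49)/(0.25√(1 − R²))), with 0.49 = 1.96 × 0.25
- power of an adjusted test ≈ Φ(d/(0.25√(1 − R²)) − 1.96)

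At d = 0.7:

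| R² | √(1 − R²) | False positives, unadjusted | Power, unadjusted | Power, adjusted |
|---|---|---|---|---|
| 0 | 1.000 | 5.0% | 80% | 80% |
| 0.1 | 0.949 | 2 × [1 − Φ(2.07)] = 3.9% | Φ(0.21/0.237) = 81% | Φ(2.95 − 1.96) = 84% |
| 0.3 | 0.837 | 2 × [1 − Φ(2.34)] = 1.9% | Φ(0.21/0.209) = 84% | Φ(3.35 − 1.96) = 92% |

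**Step 3: simulation with the tests themselves.** Mann-Whitney against a model on rank-transformed values adjusted for age and sex, under the same assumptions:

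| R² | Mann-Whitney power | Rank-based adjusted power | Loss |
|---|---|---|---|
| 0 | 77% | 77% | 0 points |
| 0.1 | 78% | 81% | 3 points |
| 0.3 | 79% | 88% | 9 points |

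The simulated Mann-Whitney false-positive rate is 3.7% at R² = 0.1, 3.1% at 0.2 and about 2% at 0.3, in line with Step 2.

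**Step 4: large difference.** At d = 1.5 and R² = 0, 1.5/0.25 − 1.96 = 4.04, so power is about 100% without adjustment. Nothing is left to gain.

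**Step 5: if matching were individual.** For 20 sets of one volunteer and four patients with within-set correlation ρ, the variance of volunteer minus mean of four patients is 1.25 × SD² × (1 − ρ). Simulated power at d = 0.7, Mann-Whitney versus signed-rank on set differences: 77% vs 73% at ρ = 0; 78% vs 76% at 0.05; 78% vs 78% at 0.10; 79% vs 82% at 0.20; 81% vs 87% at 0.30. The matched-set test loses power when the correlation is near zero and helps only from about 0.2 upward.

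**The case against.** The strongest points on the other side, and what stands of each:

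- **The loss is conditional.** A reader might infer that the standard error is too large in every case. The documents give no relation between age or sex and any reading, so this cannot be asserted. This point stands.
- **No matched sets are described.** A reader might assume 20 sets of four patients to one volunteer, under which a correlation of 0.5 would push the Mann-Whitney false-positive rate below 1%. The single line in Participants fits group-level matching at least as well. This point stands, so the sizes given here rest on frequency matching.
- **Larger losses come partly from changing the type of test.** Under normality at R² = 0.1, power is 78% for Mann-Whitney, 81% for an unadjusted t-test and 83% for an adjusted linear model. Three of those five points have nothing to do with age or sex. This stands, which is why the comparison above is with a rank-based adjusted analysis.
- **Adjustment helps without matching too.** Adjusted power is nearly the same with unmatched volunteers (83% at R² = 0.1 either way), so the gain is ordinary covariate adjustment. True. The fall of the false-positive rate below its stated level, however, comes from matching that the test ignores.
- **The difference may be large.** The Discussion links Brillouin readings to total protein concentration. If the difference is about 1.5 SD, nothing is lost. This stands.
- **A linear model can do worse.** If volunteers vary less than patients (assumed SD ratio 0.3, d = 0.5), Mann-Whitney has 80% power against 71% for an adjusted linear model on untransformed values. This stands against that model, but a rank-based or robust-SE version is no worse than Mann-Whitney there.
- **The quoted sentence is general, and the article is condensed.** The tests are not tied by name to the patient-versus-healthy comparison, and the stated primary outcome is development and validation of the method. That limits the weight of the point. Still, these are the only group-comparison tests named, and the choice offered is among tests that all ignore the matching factors.

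**Conclusion.** The point holds in conditional form. The volunteers are matched on age and gender, and the named group tests use neither. Where age or sex influences a reading, those tests are conservative and lose some power; elsewhere they lose nothing. Under the assumptions stated (d = 0.7 SD, 80 versus 20, frequency matching, normal readings), the loss is about 0 points at R² = 0, 3 at R² = 0.1 and 9 at R² = 0.3, and it disappears for a difference of about 1.5 SD.

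A reader might go further and infer biased estimates or too many false positives. The documents do not support that: the error runs only towards missed differences. This is a modest, inexpensive improvement and does not threaten the validity of the study.

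**What to change.** In the Statistical analysis section, add wording to this effect:

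*Brillouin, SERS/Raman and LC-MS readings will be compared between patients and healthy volunteers with a model adjusted for age and sex, on rank-transformed values, or with robust standard errors if the spread differs between the groups. Binary readings will be compared by logistic regression with age and sex where event counts allow. The unadjusted Mann-Whitney or Fisher result will be reported as a sensitivity analysis.*

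State also whether matching is individual or by frequency, and use a matched-set analysis only if volunteers were individually matched to identified patients.

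The cost is a few sentences, two degrees of freedom and an assumed form for age. Demographic data already go into the case report forms, so no new data or participants are needed.
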